**FIGURE 1 tme70002-fig-0001:**
[figure not shown]
Transfusion process steps under manual and BETC systems. Steps 1, 9 and 10 under the manual system will be replaced by the BETC.

PPI checks must be performed every time for steps 1 and 9. In the manual process, step 1 requires that labelling on the blood sample and the request form is handwritten, where the clinician is required to write the patient's full name, date of birth, hospital number, NHS number, date and time when the sample is taken, and provide his/her signature. For step 9, prior to blood administration, PPI must be performed by two nurses who are required to check that the patient's details on the wristband match those on the blood unit and the compatibility label that is attached to the blood unit. For step 10, clinicians must return the traceability tag attached to the blood unit from the ward to the laboratory, where an individual will enter this information in the transfusion electronic system—this confirms the fate of the unit and is called traceability.

### 
Intervention

2.2

The intervention consists of a portable handheld scanning device (or Personal Device Assistance [PDA]) and a mobile printer. For the sample labelling (step 1), the PDA obtains the patient's details electronically via scanning the patient's 2D barcode on the wristband, which is embedded with the patient's details from the patient's electronic record and, in doing so, supports PPI. The PDA then communicates via Bluetooth with the mobile printer to print the label, which is then attached to the blood sample. For blood administration (step 9), the device uses the same 2D barcode to obtain and verify the patient's details against the compatibility label attached to the blood unit. For traceability (step 10), information on the use of blood is transmitted electronically every time a unit is being transfused using the PDA. It should be noted that the BETC can only be used if patients wear wristbands; consequently, these devices will not be implemented in areas where this was not the case (e.g., the outpatient setting for group and screen [G&S] samples).

The routine clinical care of patients receiving transfusions or needing blood samples will not be altered for the purpose of this study.

### 
Theory of change

2.3

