#### Health Economics Inventory dataset

2.7.3

Two Health Economics Inventory forms were developed for the evaluation study. One form was applied in the staff training survey. Every clinician in this study was invited to complete the Health Economics Inventory form after she/he completed the BETC training. The form collected clinician‐level data on training duration, job title, years of experience in the current job, and feedback on the BETC system. The other form was used to collect data on costs for PDA devices and mobile printers, licence/software costs, and BETC system maintaining costs; material and consumable costs for G&S sample collection and labelling; salaries for BETC implementation staff and proportional salaries for two Transfusion Practitioners on the traceability task.

Figure 2 shows the linkage between outcome measures, proxies for outcome measures in various datasets, and the data sources.

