#### Cost savings within the evaluation period

2.8.2

Cost savings will be quantified by the monetary value of reduction in (1) clinician time used for completing transfusion‐related tasks and (2) transfusion‐related material and consumable use. We identified seven sources of savings for clinician time and two sources of savings for material and consumable use, as reported in Table 1.

For six (out of seven) sources of clinician time saving associated with BETC implementation, we will estimate the amount of time saved from each source by combining the time saved from one transfusion to the number of relevant transfusions. These will then be converted to monetary value by applying the hourly rate of clinicians.^21^, ^22^ Costs will be presented at 2023/24 level. For traceability, the monetary value of clinician time saved will be estimated by the proportion of salaries for two Transfusion Practitioners in Barts Health NHS Trust for their time spent on supporting the traceability of transfusions under the manual transfusion system. Regarding the two sources of cost savings in material and consumable use, for each source, we will identify and then quantify the material and consumable use items saved from one transfusion, followed by converting the quantities to monetary value by applying the unit cost for each item, and finally to estimate cost savings by combining monetary value from one transfusion to the number of relevant transfusions.

During the 2‐year implementation period, the PDA uptake did not reach 100% for many wards. Therefore, we will report two types of annual cost savings, that is, actual savings and potential savings when the maximum PDA uptake is achieved.

#### 
BECT implementation and staff training costs

2.8.3

We will report the actual implementation costs occurred at the Trust and year level. The costs include salary for implementation staff, costs for software licences, PDA hardware maintaining and software support fee, costs for PDA devices and mobile printers. Training costs for clinicians to learn how to use the PDA device will be calculated at clinician level by applying clinicians' hourly rate to the time spent on training sessions.

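### The traceability saving is valued at its manual-system baseline cost, not at the reduction achieved, so this part of the actual savings is overstated if the rule is applied as written

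*Protocol article*

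**What the plan says.** Section 2.8.2 of the protocol article sets the target quantity: "Cost savings will be quantified by the monetary value of reduction in (1) clinician time used for completing transfusion‐related tasks", together with material and consumable use. Six of the seven time sources are estimated by "combining the time saved from one transfusion to the number of relevant transfusions".

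Traceability has its own rule. Its value is the proportion of the salaries of two Transfusion Practitioners "for their time spent on supporting the traceability of transfusions under the manual transfusion system". The matching data item in section 2.7.3 is "proportional salaries for two Transfusion Practitioners on the traceability task"; the article states no corresponding measurement for the BETC period.

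The same section reports that "the PDA uptake did not reach 100% for many wards" during the two implementation years, and for that reason "we will report two types of annual cost savings, that is, actual savings and potential savings when the maximum PDA uptake is achieved".

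Sections 2.1 and 2.2 describe the work itself. Under the manual system "clinicians must return the traceability tag attached to the blood unit from the ward to the laboratory", where someone enters the information. Under BETC, "information on the use of blood is transmitted electronically every time a unit is being transfused using the PDA".

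**The concern.** A saving is a before-minus-after difference. The traceability rule supplies only the before term. It conflicts with the definition that opens its own section, and this is a formula the article states, not a detail it leaves out.

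The distinction between actual and potential savings exists because uptake was incomplete. The other six sources can reflect that through the number of relevant transfusions. The traceability rule has no term that can vary with uptake, so the same amount would be entered under both headings in each year, including for hospitals where full roll-out had not begun. That also sits badly with the Discussion, which expects the full cost savings not to be observed within the evaluation period.

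At stake is the actual-savings figure, which is meant to inform decisions on wider NHS roll-out.

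**Working it through.** **Inputs from the article**
- Definition of a saving, rule for traceability, rule for the other six sources, uptake below 100%: section 2.8.2.
- Electronic traceability only for units transfused with the PDA: section 2.2.
- Full roll-out windows (section 2.4): Hospital 1 July to November 2023, Hospital 2 December 2023 to March 2024, Hospital 3 April to October 2024, Hospital 4 November 2024 to April 2025. Counting May 2023 as month 1 and April 2025 as month 24, these are months 3–7, 8–11, 12–18 and 19–24.

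**Not given:** the salary share, the uptake figures, hospital volumes, and any traceability work that remains for PDA units. The article states no numerical saving, so there is no figure to reproduce.

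**Formula.** Let S be the annual manual-system traceability salary cost, u the share of units transfused with the PDA, and r the share of practitioner traceability work that remains for those units.
- Saving as written: S
- Net saving: S × u × (1 − r)
- Overstatement factor: 1 / [u × (1 − r)]

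The factor is 1 only when u = 1 and r = 0.

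**Illustrative values of u from the calendar.** Assumptions: equal volume in each hospital, the Haematology Day Unit pilot ignored, r = 0. The denominator is 4 hospitals × 24 months = 96 hospital-months, or 48 per year.

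*Full use from each hospital's first roll-out month:* 22 + 17 + 13 + 6 = 58 hospital-months; u = 58/96 = 0.604; factor 1.66.

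*Use only after each roll-out is complete:* 17 + 13 + 6 + 0 = 36; u = 36/96 = 0.375; factor 2.67.

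*Linear ramp within each window:* u = 49/96 = 0.510; factor 1.96.

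| Assumption | May 2023–Apr 2024: u (factor) | May 2024–Apr 2025: u (factor) | 24 months: u (factor) |
|---|---|---|---|
| From first month | 16/48 = 0.333 (3.0) | 42/48 = 0.875 (1.14) | 0.604 (1.66) |
| Linear ramp | 0.243 (4.12) | 0.778 (1.28) | 0.510 (1.96) |
| After completion | 6/48 = 0.125 (8.0) | 30/48 = 0.625 (1.6) | 0.375 (2.67) |

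**Sensitivity.** With r = 0.20, the 24-month range of 1.66 to 2.67 becomes 2.07 to 3.33. Hospital weights matter too: under full use from the first month, Hospital 1 alone would give 24/22 = 1.09 and Hospital 4 alone 24/6 = 4.0.

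**The case against.** The strongest reply is that the actual/potential sentence follows the traceability rule and exempts no source. On that reading the manual salary share is a base value, and the authors mean to scale it by the uptake they collected at ward level (section 2.4). This may well be the intention. But the text gives no such scaling, and a stated formula that omits it will be applied as stated unless it is corrected.

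Second, the full manual cost is a fair value for potential savings, because the Figure 1 caption treats step 10 as replaced by BETC. This stands, and it confines the problem to actual savings.

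Third, the rule values only the two practitioners' time. Ward time for returning tags, and any laboratory entry done by others, is not visibly valued. That omission works in the opposite direction. The upward bias is therefore clear for the practitioner-salary component, less so for traceability time as a whole.

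Three stronger readings are tempting and are not supported:
- A reader might treat the linear ramp as a ceiling on exposure and claim an overstatement of at least about twofold. It is not a ceiling: full use from each first roll-out month gives 1.66, and more weight on Hospital 1 or counting the day-unit pilot would lower the factor further.
- A reader might infer that label writing and post-administration documents are also valued gross. Section 2.8.2 uses time saved per transfusion for those sources, which is already a difference; Table 1 names what is measured and does not define the estimator.
- A reader might fault section 2.8.3 for having no line for scanning time or printed labels. That section covers implementation and training costs. Scanning time is clinician time and belongs under 2.8.2, and the inventory in 2.7.3 collects consumable costs for labelling.

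**Conclusion.** The concern holds for one item. The stated traceability rule is a manual-system baseline cost, contradicts the section's own definition of a saving, and cannot separate actual from potential savings. Because manual traceability continued for units given without a PDA, the practitioner-salary component of actual savings is overstated when the rule is applied as written.

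The size cannot be determined from the document. The illustrative range of about 1.7-fold to 2.7-fold over 24 months rests on the three assumptions stated above and is not a strict bound. The distortion is larger in the first implementation year than in the second.

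The scope is limited: a share of two salaries, one of seven time sources, with no bearing on the patient-benefit analyses. It should still be corrected before the savings are reported.

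**What to change.** Rewrite the traceability sentence in section 2.8.2 so that actual and potential savings have separate rules.

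- **Actual savings, preferred:** the value of practitioner time on traceability under the manual system minus that under BETC.
- **Actual savings, if only the manual share was recorded:** the manual-system cost multiplied by the proportion of transfused units traced electronically by PDA, by hospital and year. BloodTrack Manager holds data on PDA use and Winpath holds units transfused (section 2.7.1). The salary cost is Trust-wide, so a hospital breakdown needs it apportioned, for example by units transfused. State that this version assumes traceability work falls in proportion to PDA use and that none remains for PDA units.
- **Potential savings:** keep the full manual-system cost at maximum uptake, stating the assumption that step 10 is then fully replaced.

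The cost is a change of wording plus either one further inventory question or a proportion from data already collected. The downside for the authors is that the reported actual saving becomes smaller.

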#### Benefits to patients beyond the evaluation period

2.8.4

In the UK NHS, transfusion‐related mortality and serious morbidity are rare. Therefore, the immediate impact of BETC implementation on these outcomes is likely to be limited during the implementation period. To assess potential benefits beyond the evaluation timeframe, we will review data from the national hemovigilance scheme, which provides records of all reactions and complications because of ABO‐incompatible transfusions in the UK between 1997 and 2023. We will also conduct a focused literature search to identify published disutility weights for quantifying the impact of adverse events, as a result of mismatched transfusions, on patients' quality‐of‐life. Combining together the national hemovigilance scheme data and disutility weights, we will provide an estimate of the potential long‐term health benefits to patients by reducing preventable transfusion‐related errors across the UK NHS through implementing interventions like the BETC.

We will follow CHEERS guidelines^23^ when reporting the health economic evaluation. All analyses will be conducted using the statistical software STATA 18.^24^

## DISCUSSION

3

There is considerable pressure worldwide to control the steady increase in the cost of blood transfusion. In transfusion, the costs to deliver the service exceed the costs of the blood products.^25^, ^26^, ^27^ There is limited empirical evidence on interventions that aim to manage the costs of blood transfusion as well as the economic analyses on those interventions.^28^, ^29^

BETC was developed under the strong need for technological advancements to improve transfusion safety. It is expected that the intervention will generate cost savings by freeing up clinicians' time and reducing material and consumable use. Although BETC has been proved to enhance transfusion safety in a few studies,^14^, ^15^, ^17^ the costs aspect of this intervention is unknown. By evaluating the replacement of manual transfusion processes with BETC, this study aims to fill in the literature gap by assessing the benefits of implementing the system to patients and cost savings for the NHS in one of the largest Trusts in the UK. A strength of our study is the detailed level of data collection and, as a result, the large sample size of the linked dataset. The electronic transfusion datasets provide data at the patient level for their transfusion activities. Our study will be the largest health economic evaluation of the electronic transfusion system in the world. Furthermore, we will be able to link the electronic transfusion datasets and the two datasets that were developed specifically for this evaluation study (i.e., process mapping and Health Economics Inventory). The linked dataset provides a unique opportunity for our evaluation to capture a wide range of outcomes as the results of BETC implementation, such as benefits to patients and health professionals and cost savings for hospitals and the NHS. Last but not least, we adopted a micro‐costing approach to collect detailed clinician time spent, resource utilisation, and unit cost data. This methodological choice will enable us to generate accurate estimates of BETC‐related costs and cost savings.

Our evaluation has limitations. The main limitation of the implementation study is the non‐randomised study design. We considered a randomised design at an early stage, but implementing randomisation in real life in transfusion would have been impossible. We opted for a non‐randomised, staggered, multi‐phase implementation design. Our evaluation will address these key features of the implementation. For example, we will apply for a multiple baseline interrupted time series analysis which accounts for the degree of BECT uptake to evaluate the impact of BECT implementation on mislabelled samples. While at the end of the evaluation period all wards within a hospital will have had the electronic devices, the full uptake by clinicians will take months or even longer to achieve. Therefore, we expect hospitals to be at different stages of the BECT uptake during the evaluation period, with Hospital 1 likely to have the highest uptake rate, while Hospital 4 has the lowest. As a result, in this evaluation study, we will not observe the full benefits to patients and cost savings to the NHS. However, based on transfusion activity data, process mapping data, and Health Economics Inventory data, we will estimate the full benefits.

While most hospitals in the UK currently apply the manual blood transfusion system, our evidence from this evaluation will not only generate empirical evidence for its implementation at the Barts Health NHS Trust but also support decision‐making for the technology's wider roll‐out in the UK NHS.

## Data Availability

Not applicable. This paper is a study protocol which does not involve data or data analysis.
